#### TBT group

The TBT treatment will be administered by a doctor of Korean Medicine with at least one year of clinical experience in the relevant field, following a standardized three-step process: To initiate treatment, the balance of the TMJ is assessed along three spatial axes—left-right (X), front-back (Y), and up-down (Z)—to detect any deviation. The primary goal is to determine a mandibular position that facilitates optimal alignment of the cervical spine, thereby stabilizing the positional relationship between the mandible and the maxilla. This process begins with a series of clinical assessments, including the restricted cervical rotation test, lateral cervical tension test, and cervical palpation, to evaluate bilateral muscle tension and cervical mobility. To assist in identifying the optimal balance point, a 1.6 mm-thick silicone bar (Jin Biotech, Cheonan, Korea) is used to establish an appropriate freeway space. The optimal mandibular position is defined as the position in which cervical rotation becomes smooth and symmetrical. This individualized assessment is essential for the fabrication of a CBA, which is used in the next step to temporarily fix the mandible in its ideal three-dimensional balance position.

Once the optimal mandibular position is identified, a CBA is fabricated to temporarily fix the jaw in that position. At this position, the CBA is created using a combination of two addition-type polyvinyl silicone impression materials (Exafine Putty, GC Dental Products Corp., Japan). While the patient is biting the silicone bars with both molars, the mixed impression material is molded directly onto the teeth to capture the correct mandibular position. After sitting for approximately 1 ~ 2 min, the hardened appliance (CBA) is ready for clinical use [26].

While the patient is wearing CBA, myofascial release will be performed 1 to 3 times. The practitioner will confirm the fascial relaxation response through palpation. This will be followed by a standardized set of jaw stretching exercises, which will be performed 5 times to enhance jaw mobility and relaxation [26].

#### TENS group

TENS will be administered to the control group. The procedure will be performed by a licensed Korean Medicine doctor with at least one year of clinical experience. The silicone electrode pads will be attached to the masseter muscle area on the affected side. If pain is present bilaterally, both sides will be treated. Low-frequency stimulator, H-3000-P (Hanil TM Co., Ltd., Korea), will be used for the stimulation. The stimulation frequency will be set at 3 Hz, and the intensity will be set so that the participant perceives a sensory stimulation without experiencing excessive muscle contraction or pain. Each TENS session will last for 15 min.

### Outcome measures

#### Primary outcome: visual analog scale

The primary outcome measure is the average temporomandibular joint pain Visual Analog Scale (VAS, 100 mm) score over the past week. It will be assessed at Week 0 (Baseline) and Week 6 (Primary endpoint).

#### Secondary outcomes

##### Vertical mandibular opening

The functional opening capacity of the TMJ will be evaluated by measuring both the pain-free opening and the maximum unassisted opening in millimeters (mm). Measurements will be taken at baseline, week 6, and week 10. Changes across these time points will be compared to assess improvements in TMJ range of motion and pain reduction.

##### Jaw functional limitation scale-8 (JFLS-8)

The JFLS-8 is an 8-item questionnaire that assesses the degree of jaw functional limitation in daily activities such as chewing, speaking, and facial expression. Each item is scored on a 0–10-point scale, with higher scores indicating greater limitation. Changes in total scores from baseline to weeks 6 and 10 will be analyzed to evaluate the persistence of treatment effects.

##### DC/TMD chronic pain grade scale 2.0

This scale comprehensively measures the severity of chronic pain related to temporomandibular disorders, including pain intensity, functional impact, and psychological factors. Grades will be assessed at baseline, week 6, and week 10, and changes over time will be analyzed to determine the effectiveness of pain management.

##### Treatment expectancy scale

Patients’ expectations regarding the effectiveness of treatment will be measured using a Likert scale (e.g., 1–5 points). The differences between pre-treatment expectations and actual experiences at weeks 6 and 10 will be compared to assess treatment satisfaction and the relationship between expectation and outcome.

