#### Blinding

This clinical trial will be conducted in an assessor-blinded (single-blind) manner. The outcome assessors will remain blinded to group assignments until the completion of the trial, while participants and treating investigators will be aware of the assigned interventions (TBT or TENS). The investigators responsible for outcome assessment will not participate in the randomization process and will not be informed of the group allocation or the type of intervention the participant receives.

The interventions for both the TBT and TENS groups will be performed under standardized procedures and in similar environments to minimize bias. Subject identification codes will be designed to prevent assessors from distinguishing the assigned group. The assignment and management of identification codes will be handled by the study staff and will not be disclosed to the assessors until the trial is complete, except in emergencies where unblinding is necessary for participant safety. All procedures for randomization, allocation, and blinding will be thoroughly documented to ensure transparency and reproducibility.

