#### Secondary outcome analysis

The secondary outcomes include average TMJ pain VAS scores, worst TMJ pain VAS scores, vertical temporomandibular joint opening, including pain-free opening and maximum unassisted opening, JFLS-8 scores, GCPS 2.0 scores, Treatment Expectancy Scale scores, PGIC scores at 0, 6, and 10 weeks. For continuous outcomes measured at multiple time points (e.g., VAS scores at 0, 6, and 10 weeks), linear mixed models will be used to assess within-group and between-group changes over time. Categorical outcomes will be analyzed using chi-square tests.

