However, several practical and operational difficulties must be examined during this trial. As a single-center study, the generalizability of our findings to a larger population or different clinical settings might be limited. We intend to address this by clearly defining inclusion and exclusion criteria to ensure a homogeneous patient population. To further address the generalizability, our research team is also planning a multi-center registry study, a prospective observational study, involving various Korean medical clinics and hospitals that currently implement TBT. This will allow for the collection of real-world data from a more diverse patient population and across different clinical environments, thereby enhancing the external validity of TBT’s effects.

Participant and practitioner blinding is not feasible given the nature of the interventions, which could introduce some performance or detection bias. To address this, we have implemented assessor blinding for all outcome measurements and standardized treatment protocols to ensure consistency in intervention delivery. However, it is important to acknowledge that the lack of participant and practitioner blinding might lead to differential treatment expectancy or performance bias between groups, potentially influencing subjective outcomes. While objective measures are less susceptible, the interpretation of patient-reported outcomes (e.g., VAS, PGIC, Treatment Expectancy Scale) should consider this limitation.

In conclusion, this protocol describes a meticulously designed randomized controlled trial that will provide crucial evidence on the efficacy, safety, and economic viability of TBT for TMD. The findings are expected to inform future clinical practice guidelines, particularly those related to Korean medicine interventions for TMD, and offer valuable insights for clinicians and policymakers seeking effective and sustainable treatment strategies.

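### The expectation-minus-experience difference cannot show how expectation relates to outcome, because expectation is one of its two terms; an arm contrast on it would also absorb any arm gap in expectation

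*Protocol article*

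**What the plan says.** The Treatment expectancy scale section, under Secondary outcomes, describes a Likert rating, with 1 to 5 points given as an example. It then fixes the quantity to be analysed: "The differences between pre-treatment expectations and actual experiences at weeks 6 and 10 will be compared to assess treatment satisfaction". The same sentence states what this quantity is for: "to assess treatment satisfaction and the relationship between expectation and outcome".

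The Secondary outcome analysis section includes the scale in its list, "Treatment Expectancy Scale scores, PGIC scores at 0, 6, and 10 weeks". For continuous outcomes measured repeatedly it says that "linear mixed models will be used to assess within-group and between-group changes over time", and it gives chi-square tests for categorical outcomes. It does not say which of the two applies to this item.

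The Blinding section states that participants know their treatment. The Discussion adds that "the lack of participant and practitioner blinding might lead to differential treatment expectancy or performance bias between groups", and asks that patient-reported results, this scale included, be read with that in mind. No section plans to analyse the experience rating on its own or adjusted for expectation, or to relate expectation directly to an outcome.

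**The concern.** Write E for the pre-treatment expectation, X for the later experience rating, and D = X − E. Two problems follow from using D for the stated aims.

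1. **Expectation-outcome relationship.** E sits inside D with a minus sign. Relating D to E therefore yields a strong association even when E and X have nothing to do with each other, and it can turn a true positive relation into a negative one.
2. **Comparison between arms.** The arm difference in D is the arm difference in X minus the arm difference in E. Two arms with the same experience will differ on D by exactly the gap in what they expected.

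Participants are unblinded and the primary outcome is self-reported pain. Information on how expectation relates to outcome would help in interpreting the result, and this is the only place where the article plans to look at it.

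**Working it through.** **The plan's own figure.** The article gives no figure for this score. The only related number is the sample size: 2 × (1.96 + 1.28)² × 1.5² / 2² = 11.81, rounded to 12 per arm. With 20% dropout, 12 / 0.8 = 15 per arm, 30 in total. This reproduces, and it sets the sizes used below: 12 to 15 per arm, 24 to 30 overall.

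**Inputs not in the article.** The SDs of E and X, their correlation ρ, and any arm gap in expectation are assumptions and are shown as ranges.

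**Step 1: coupling.** In general

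corr(E, D) = (ρ·s_X − s_E) / √(s_E² + s_X² − 2ρ·s_E·s_X).

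With ρ = 0 this is −s_E / √(s_E² + s_X²):

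| s_E / s_X | corr(E, X − E) when E and X are unrelated |
|---|---|
| 0.5 | −0.45 |
| 1 | −0.71 |
| 2 | −0.89 |

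With equal SDs the formula reduces to −√((1 − ρ)/2):

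| True ρ | corr(E, X − E) |
|---|---|
| 0 | −0.71 |
| 0.3 | −√0.35 = −0.59 |
| 0.5 | −√0.25 = −0.50 |

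A real positive relation thus appears as a negative one, and a stronger real relation looks weaker. Taking E − X instead changes only the sign.

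Simulation with independent 1-to-5 Likert scores (a uniform and a skewed distribution, 24 and 30 participants, 20,000 replicates each) gave a mean correlation of about −0.70. The test of E against D reached p < 0.05 in 98% to 99.9% of trials. Testing E against X directly gave about 5%.

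**Step 2: arm contrast.** If the mixed model is applied to this scale, with expectation as the week-0 value and experience as the later value, the group-by-time term for complete data is the arm difference in mean D. That equals (arm difference in X) − (arm difference in E). Set the first bracket to zero and let the arms differ in E by g points. With SD 1 for each rating, the SD of D is √(2 − 2ρ): 1.414 at ρ = 0 and 1.183 at ρ = 0.3. The noncentrality is g / (SD_D · √(2/n)). Two-sided 5% t-test:

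| Gap g | n per arm | ρ = 0 | ρ = 0.3 |
|---|---|---|---|
| 0.5 | 12 | 13% | 17% |
| 0.5 | 15 | 15% | 20% |
| 1.0 | 12 | 38% | 51% |
| 1.0 | 15 | 46% | 61% |

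At g = 0 the rate is the nominal 5%.

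**Step 3: the alternative.** Comparing X between arms with E as a covariate, simulated at ρ = 0 with gaps from 0 to 1 point and 12 or 15 per arm, rejected in 4% to 6% of trials at every gap.

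**The case against.** The strongest reply is that the article names no test. It says the differences will be compared; it does not say that expectation will be correlated with the difference, or that the difference will be contrasted between arms. The mixed model is assigned to continuous outcomes, and a 5-point item might be treated as categorical. Such details may stand in the full protocol or an analysis plan, neither of which is shown. This stands, and it is why both consequences are conditional. It does not remove the point: the article does choose the quantity and does assign it to the expectation-outcome question, and that choice is unsuitable whichever test follows.

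A reader might infer that the arm comparison is certainly biased against the arm that expected more. The documents do not support that. The Discussion says only that lack of blinding might produce differential expectancy. The rating is described as pre-treatment, the envelope is opened in front of the participant, and the order of the two cannot be read from the text shown. If expectation is rated before allocation is known, an arm gap is chance imbalance and there is no systematic bias. If it is rated afterwards, the gap could be systematic.

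A reader might also infer that the difference score is worthless. It is not: as a description of whether expectations were met it is legitimate, and on that definition an arm that expected more and experienced the same is indeed less satisfied. Finally, the rejection rates in Step 2 depend on an assumed SD, correlation and gap, and are illustrations only.

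**Conclusion.** The concern holds as a badly chosen derived score for one secondary item. The expectation-experience difference cannot assess the relationship between expectation and outcome, because any analysis relating it to expectation is coupled: |r| is about 0.71 with no true relation and equal SDs, and 0.45 to 0.89 over SD ratios of 0.5 to 2. This part needs no assumption about timing.

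The second part is conditional on the score being compared between arms. An arm gap in expectation then enters the contrast in full. The inflation to 13–20% at 0.5 point and 38–61% at 1 point rests on SD 1, correlation 0 to 0.3, 12 to 15 per arm and equal experience. Whether such a gap would be systematic turns on the timing of the rating, which the documents do not show. The point is minor in weight: the primary ANCOVA and the sample size are untouched.

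**What to change.** In the Treatment expectancy scale section, with a matching line in Secondary outcome analysis:

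- Assess the expectation-outcome relationship by regressing week-6 VAS, and separately week-10 VAS, on pre-treatment expectation, arm and baseline VAS.
- For any between-arm comparison, compare the week-6 and week-10 experience ratings with pre-treatment expectation as a covariate.
- Keep the expectation-experience difference only as a descriptive measure of met expectations, without a test.
- Report whether expectation was recorded before or after allocation was disclosed.

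The cost is a wording change and one additional model on data already planned for collection. Estimates will be imprecise with 24 to 30 participants and should be presented with intervals. Recruitment was scheduled from February to June 2025, so the order of questionnaire and envelope may no longer be open to change; the analysis change does not depend on it.

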##### Patient global impression of change (PGIC)

The PGIC is a 7-point scale used to evaluate the patient’s overall perception of improvement or worsening in health status (1 = very much worse, 7 = very much improved). Changes in PGIC scores at weeks 6 and 10 will be analyzed to assess the subjective effectiveness of the intervention.

### Safety assessment

For safety assessment, the occurrence of adverse events (AEs) and their potential relationship with the intervention (TBT or TENS in the control group) will be evaluated. The safety of the intervention methods will also be assessed through the measurement of vital signs and participant interviews regarding any discomfort or safety concerns experienced following the intervention. Both vital signs and AEs will be monitored and assessed at each visit from weeks 1 to 6, as well as at the follow-up visit in week 10.

The criteria and methods for safety evaluation include the documentation of all AEs and vital signs. Safety assessments will be conducted for all participants enrolled in the study (the intention-to-treat (ITT) population). Any undesirable medical findings or symptoms not observed before the start of the clinical trial will be classified as AEs.

In preparation for any adverse symptoms that may arise during the study period, appropriate medical actions will be taken if any new symptoms, not observed before the initiation of the clinical trial, occur. The investigators will record the date of onset, severity, outcome of the AE, actions taken regarding the intervention, the causal relationship between the AE and the intervention, any other suspected medications, and treatments provided for the AE. The principal investigator will ensure continuous follow-up until the AE resolves or the participant’s condition stabilizes.

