### Sample size calculation and statistical hypotheses

The sample size for this trial was determined based on statistical calculations and reference to a previous randomized controlled trial with a similar design [25]. A total of 30 participants (15 in the intervention group and 15 in the control group) will be recruited, considering a 20% dropout rate. This allows for 24 evaluable subjects (12 per group) for the primary analysis.

The hypothesis of this study is as follows:$$\mathrm{H}_o\left(\text{null hypothesis}\right):\mu\mathrm{t}=\mu\mathrm{c}$$$$\mathrm{H}_1\left(\text{alternative hypothesis}\right):\mu\mathrm{t}\neq\mu\mathrm{c}$$

µt denotes the mean change in Visual Analog Scale (VAS, mm) score from baseline to 6 weeks in the experimental group (TBT), and µc is the mean change in VAS (mm) score from baseline to 6 weeks in the control group (TENS). The experimental and control groups will be recruited in a one-to-one ratio.

The calculation assumed a two-sided significance level (α) of 0.05, a type II error (β) of 0.1 (power = 90%), and a 1:1 allocation ratio. A previous RCT with a similar design (10-week intervention, 12 sessions) reported a mean difference of − 2.53 in VAS between groups, with a pooled standard deviation (SD) of 0.96 (Rezaie et al., 2022). For conservative estimation, this study applied a smaller mean difference (–2) and larger SD (1.5).

The required sample size per group was calculated using the formula for a two-sample t-test:

Calculation formula: $$\:\frac{2{({z}_{1-\frac{\alpha\:}{2}}+{z}_{\beta\:})}^{2}\times\:{\sigma\:}^{2}}{\left|{\mu\:}_{T}-{\mu\:}_{c}\right|}=\:\frac{2{(1.96+1.28)}^{2}\times\:{1.5}^{2}}{{(-2)}^{2}}=11.81\approx\:12$$  

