### Assignment of interventions

#### Allocation

The randomization process will be managed by a statistician who is not involved in the conduct or assessment of the clinical trial. The randomization officer will generate the randomization list using a specifically planned and reproducible method, employing Python 3.12.4 (Python Software Foundation, Wilmington, DE, USA) to ensure equal probability of assignment for each participant. Block randomization will be used to maintain balance between groups, with participants allocated to the intervention (TBT) and control (TENS) groups in a 1:1 ratio.

The randomization list will be sealed and stored in a manner that allows confirmation of whether the seal has been broken, and will be managed separately by the principal investigator. For allocation, the study coordinator will open the randomization envelopes sequentially in front of the participant at the time of assignment. Each opened envelope will have the date of opening and the study coordinator’s signature recorded and will be stored separately for documentation.

Participants who provide written informed consent and undergo screening will be assigned a screening number in the format DJ-S-001 (where DJ refers to Daejeon University Daejeon Korean Medicine Hospital, S indicates Screening, and 001 is the serial number). Only those who meet the inclusion and exclusion criteria after the eligibility assessment will be assigned a subject identification code in the format DJ-E-001 (where E indicates Enrollment).

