### Statistical analysis

The primary analysis will be performed on the FAS, which will be defined under the ITT principle. In this study, all randomized participants will be analyzed as allocated, except for those who (1) do not meet major inclusion criteria, (2) never receive any intervention specified in the protocol, or (3) have no post-randomization data due to lack of any assessment. The PP set will include participants who complete the study without major protocol violations, such as premature discontinuation of the intervention, violation of inclusion/exclusion criteria, overall intervention compliance below 66.6%, or other significant protocol deviations.

The efficacy of the intervention will be primarily evaluated using the FAS population, with supportive analyses conducted on the PP set. In the event of missing data, the amount and mechanism of missingness will be assessed, and appropriate imputation methods will be selected and applied. All statistical tests will be two-sided, with a significance level of 5%. For all primary and secondary outcomes, point estimates of treatment effects and their corresponding 95% confidence intervals (CIs) will be reported. Effect sizes (e.g., Cohen’s d for continuous variables) will also be presented where appropriate to indicate the magnitude of the observed effects.

Demographic and baseline clinical characteristics will be summarized by treatment group. Continuous variables will be presented as means and standard deviations, and analyzed using Student’s independent t-test or Wilcoxon rank-sum test, depending on normality. Categorical variables will be summarized as frequencies and percentages, and analyzed using Pearson’s chi-squared test or Fisher’s exact test, as appropriate.

All statistical analyses will be performed using Python (version 3.12.4) with its statistical libraries, including statsmodels and scipy. The random assignment will also be conducted using Python (version 3.12.4).

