#### Primary outcome analysis

The primary outcome, the mean change in TMJ pain VAS from baseline to Week 6 between the TBT and TENS groups, will be analyzed using an Analysis of Covariance (ANCOVA), with the baseline VAS score included as a covariate. The primary analysis will be conducted on an intention-to-treat (ITT) basis, including all randomized participants. In the event of missing values, multiple imputation using chained equations will be employed, assuming data are missing at random (MAR).

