#### Safety analysis

AEs will be recorded at each visit through spontaneous reporting and systematic questioning. The incidence, severity, and causality (relatedness to intervention) of AEs will be summarized using descriptive statistics and compared between groups using Fisher’s exact test or chi-square test.

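### AE incidence is tied to everyone enrolled, so any participant who is never treated would dilute that arm's rate; a treated-participant denominator should be stated

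*Protocol article*

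**What the plan says.** The Safety assessment section of the protocol article names its population directly: "Safety assessments will be conducted for all participants enrolled in the study (the intention-to-treat (ITT) population". AEs and vital signs are to be checked at the visits in weeks 1 to 6 and at week 10.

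The Safety analysis section says what is done with the events. Incidence, severity and causality are "summarized using descriptive statistics and compared between groups using Fisher’s exact test or chi-square test". It names no population of its own.

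Three other places bear on what that population contains:

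- Primary outcome analysis shows how the article uses the term ITT: "The primary analysis will be conducted on an intention-to-treat (ITT) basis, including all randomized participants".
- Allocation gives the enrolment code once eligibility is confirmed: "Only those who meet the inclusion and exclusion criteria after the eligibility assessment will be assigned a subject identification code". Having started treatment is not a condition.
- Statistical analysis, in defining the full analysis set (FAS), removes among others those who "never receive any intervention specified in the protocol".

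No set restricted to treated participants is defined for safety anywhere in the article.

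**The concern.** The efficacy set drops people who were never treated, while the population named for safety keeps them. That is the reverse of what the two analyses usually need. AE incidence is meant to describe what happens to people exposed to TBT or TENS. A person who leaves before the first session has no exposure and, because AEs are gathered at treatment and follow-up visits, little opportunity to report anything. Left in the denominator, that person counts as event-free and pulls the arm's incidence down.

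At stake is the accuracy of the AE rates in a small trial whose aims include safety. If the two arms had different numbers of non-starters, the between-arm comparison would also be affected. Such a difference is possible, because the envelope is opened in front of the participant and participants know their arm. Nothing in the article shows that it will occur.

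**Working it through.** **Inputs.** Sample size calculation and statistical hypotheses gives the arm size and the dropout allowance: "A total of 30 participants (15 in the intervention group and 15 in the control group) will be recruited, considering a 20% dropout rate". The number never treated in an arm, *k*, is not given. It is treated here as an assumption running from 0 to 3.

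**The plan's own figure.** 2 × (1.96 + 1.28)² × 1.5² / 2² = 11.81, rounded up to 12 per arm. Allowing for 20% dropout, 12 / (1 − 0.20) = 15 per arm, or 30 in total. Both stated figures reproduce, so the enrolled AE denominator is 15 per arm and the allowance is 15 − 12 = 3 per arm.

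**Dilution of one arm's incidence.** Let *x* treated participants have an AE, and assume no events are recorded in the never-treated. The enrolled-set incidence is *x*/15 and the treated-set incidence is *x*/(15 − *k*). Their ratio is (15 − *k*)/15, a relative reduction of *k*/15 whatever *x* is. With *x* = 3:

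| *k* | Enrolled set | Treated set | Relative reduction |
|---|---|---|---|
| 0 | 3/15 = 20.0% | 3/15 = 20.0% | 0% |
| 1 | 3/15 = 20.0% | 3/14 = 21.4% | 6.7% |
| 2 | 3/15 = 20.0% | 3/13 = 23.1% | 13.3% |
| 3 | 3/15 = 20.0% | 3/12 = 25.0% | 20.0% |

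**Between-arm test, equal loss.** Take 3 events against 0.

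- 15 per arm: two-sided Fisher p = 2 × C(15,3)/C(30,3) = 2 × 455/4060 = 0.224.
- 12 per arm: 2 × C(12,3)/C(24,3) = 2 × 220/2024 = 0.217.

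The test hardly moves.

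**Between-arm test, unequal loss.** Take 5 events against 0, with non-starters only in the arm that has the events.

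- 15 v 15 (enrolled set): p = 2 × C(15,5)/C(30,5) = 2 × 3003/142506 = 0.042.
- 14 v 15 (*k* = 1): p = C(14,5)/C(29,5) = 2002/118755 = 0.017.
- 12 v 15 (*k* = 3): p = C(12,5)/C(27,5) = 792/80730 = 0.0098.

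Part of this fall is an artefact of Fisher's test. Once the arms differ in size, the opposite extreme table is more probable than the observed one and no longer counts towards the two-sided p. On one tail, 0.021 becomes 0.017 or 0.0098. The shift is visible, but in these examples p stays below 0.05 throughout.

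**The case against.** The best defence is that Safety assessment describes who is monitored, and monitoring everyone enrolled is sound. Safety analysis, where the test is planned, names no denominator. This has some force. But the parenthesis in Safety assessment names an analysis population, and it is the only one the article offers for safety.

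A second defence is that the ITT label may be loose for the FAS, which is framed as an ITT set and already drops the never-treated. On that reading there is no dilution. The reference to everyone enrolled, and the article's use of ITT elsewhere for all randomised participants, go against it. If it was intended, the safety sentence still needs correcting.

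Several stronger readings are tempting, and the article does not support them:

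- *Safety will be analysed by assigned arm.* The safety text does not say so. The rule that "all randomized participants will be analyzed as allocated, except for those who" belongs to the FAS definition, and nothing in the article foresees a participant receiving the other arm's treatment. The dilution does not depend on this inference.
- *Non-starters are expected.* The FAS definition provides for them but predicts none.
- *A 20% understatement is the likely size.* That needs all dropout to fall before the first session. The allowance covers the trial as a whole, with 12 sessions and a week-10 visit.
- *The between-arm test will be distorted.* With equal loss it barely changes. Only unequal loss matters much, and the article gives no figure for that.
- *Upper confidence limits for zero events will be too low.* With 1 − 0.05^(1/n), the one-sided 95% limit is 18.1% at n = 15 and 22.1% at n = 12. The arithmetic is right, but the article plans no such limit for AEs.
- *Harm would be hidden.* All AEs are to be documented with onset, severity and causality, and a treated-only rate could be worked out from the same data.

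An analysis plan or the full protocol may define the set more precisely. That would not make the sentence printed here right.

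**Conclusion.** The point holds in conditional form. The article names all enrolled participants as the safety population, gives no other denominator for the AE comparison, and excludes never-treated people from efficacy only. If any participant is never treated, that arm's AE incidence is understated by 6.7% in relative terms per person. The range is 0% (everyone starts) to 20% (all 3 of the arm's dropout allowance leave before the first session). The between-arm comparison is at risk mainly if non-starters are unequal. These figures assume 15 per arm and no recorded events in the never-treated, and the number of non-starters is an assumption throughout. The importance is low, but the correction is simple.

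**What to change.** Keep AE recording for everyone enrolled. In both Safety assessment and Safety analysis, state that AE incidence and the between-group comparison use participants who received at least one TBT or TENS session, grouped by the intervention received should that ever differ from allocation. List any event in a never-treated participant separately, so that nothing is lost. Remove the ITT label from the safety sentence.

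The cost is about a sentence in each section. Session attendance must already be known in order to apply the never-treated exclusion from the FAS and the 66.6% compliance rule for the per-protocol set, so no new data are needed. The definition should be recorded before outcome data are analysed.
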